## Abstract

**Background:**

There are identified gaps in the care provided to children with cancer based on the self-identified lack of education for health care professionals in pediatric palliative care and in the perceptions of bereaved parents who describe suboptimal care. In order to address these gaps, we will implement and evaluate a national roll-out of *Education in Palliative and End-of-Life Care for Pediatrics* (EPEC®-Pediatrics), using a ‘Train-the-Trainer’ model.

**Methods/design:**

In this study we are using a pre- post-test design and an integrated knowledge translation approach to assess the impact of the educational roll-out in four areas: 1) self-assessed knowledge of health professionals; 2) knowledge dissemination outcomes; 3) practice change outcomes; and 4) quality of palliative care. The quality of palliative care will be assessed using data from three sources: a) parent and child surveys about symptoms, quality of life and care provided; b) health record reviews of deceased patients; and c) bereaved parent surveys about end-of-life and bereavement care. After being trained in EPEC®-Pediatrics, ‘Master Facilitators’ will train ‘Regional Teams’ affiliated with 16 pediatric oncology programs in Canada. Each team will consist of three to five health professionals representing oncology, palliative care, and the community. Each team member will complete online modules and attend one of two face-to-face conferences, where they will receive training and materials to teach the EPEC®-Pediatrics curriculum to ‘End-Users’ in their region. Regional Teams will also choose a *Tailored Implementation of Practice Standards* (TIPS) Kit to guide implementation of a quality improvement project in their region; support will be provided via quarterly meetings with Co-Leads and via a listserv and webinars with other teams.

**Discussion:**

Through this study we aim to raise the level of pediatric palliative care education amongst health care professionals in Canada. Our study will be a significant step forward in evaluation of the impact of EPEC®-Pediatrics both on dissemination outcomes and on care quality at a national level. Based on the anticipated success of our project we hope to expand the EPEC®-Pediatrics roll-out to health professionals who care for children with non-oncological life-threatening conditions.

**Electronic supplementary material:**

The online version of this article (doi:10.1186/s12904-016-0085-8) contains supplementary material, which is available to authorized users.

## Background

Despite significant improvements in treatment, childhood cancer remains a leading cause of non-accidental death in children beyond infancy [1]. Annually in Canada, about 10,000 children are living with cancer (both those receiving cancer treatments and long-term survivors) and approximately 210 will die from their disease [2]. Even when a child survives, from the moment of diagnosis the threat of death may be foremost in the mind of the parents, siblings, and ill child. The treatments aimed at achieving survival are generally intensive with a significant symptom burden that is often long-lasting and disruptive to the life of the child and family [3].

Palliative care for children focuses on alleviating the physical, social, psychological, and spiritual suffering experienced by children and families, while promoting quality of life, fostering family connections, and sustaining hope despite the possibility of death. It is a family-centered approach that includes shared decision-making and sensitivity to the family’s cultural and spiritual values, beliefs, and practices [4]. In relation to pediatric cancer, palliative care has historically been thought of as being relevant only once all treatments with curative intent have been discontinued, and is offered as an alternative rather than a concurrent treatment [5]. However, emerging data suggest that principles of palliative care can and should be incorporated from diagnosis and throughout the disease course, not only at the end of life, to ensure relief of suffering and good quality of life regardless of the disease outcome [6–10]. Consultation from specialist palliative care teams may be helpful for more complex situations [3].

Oncologists and other health professionals report receiving little training specific to pediatric palliative care (PPC) [11–13]. This lack of training may contribute to reports of less than optimal care in this area: parents’ report that children with cancer experience a great deal of suffering from pain and other symptoms left inadequately treated [14, 15]; some parents feel abandoned by health professionals both before and after their child’s death [16, 17]; family-centered care is not uniformly practiced [12]; and siblings’ needs are not always adequately addressed [12, 18]. To realize improvements in these areas, it is crucial that all health professionals who provide care to children with cancer receive comprehensive education about PPC as well as guidance and support to implement new knowledge and skills throughout the disease course. Moreover, efforts are needed to enhance collaboration between pediatric oncology and specialists in PPC. Such efforts will build familiarity, trust, and relationships, thereby facilitating concurrent delivery of disease-directed and palliative care to children living with cancer [3]. To achieve these goals, we will implement a national roll-out of *Education in Palliative and End-of-Life Care for Pediatrics* (EPEC®-Pediatrics) [19], a curriculum specifically designed for pediatric physicians and advanced practice nurses using a ‘Train-the-Trainer’ model.

Built on the demonstrated success of the original EPEC™ curriculum [20], focused on care of adults, EPEC®-Pediatrics combines didactic sessions, video presentations, interactive discussions, and practice exercises. It is comprised of 24 modules that can be taught face-to-face to interprofessional End-Users by EPEC®-Pediatrics Trainers. The Trainers learn the content via 19 online modules plus 5 delivered at a one and a half day in-person conference by EPEC®-Pediatrics Master Facilitators demonstrating effective adult teaching. Funded by a US$ 1.6 million National Institutes of Health/National Cancer Institute (1 R25 CA151000-01) grant from 2010-2015, [name] et al. developed the curriculum in collaboration with 35 national and international leaders in the field of paediatric pain medicine, hematology/oncology and palliative care as well as parent advisors [21]. A list of the modules is provided in Table 1. Following initial development, the curriculum was refined between 2012 and 2014 based on a beta testing conference and three subsequent Train-the-Trainer conferences with 200 pediatric physicians and advanced practice nurses in the United States and 19 other countries. All EPEC®-Pediatrics content is evidence-based and is delivered according to effective adult-education pedagogy. EPEC®-Pediatrics uses a Train-the-Trainer model; participants learn the content as well as obtain effective strategies and resources to educate others. In a recent systematic review, use of a Train-the-Trainer model was shown to be effective in improving knowledge and skills of health professionals, enhancing dissemination, and having a positive impact on patient outcomes [22].

**Table 1 Tab1:** EPEC®-Pediatrics modules

	Title	Mode of delivery^a^
1	Pediatric Palliative Care: Why Does it Matter	Online
2	Child Development	Online
3	Family Centered Care	Online
4	Grief and Bereavement	Online
5	Self-Care for Professionals	Face-to-Face
6	Team Collaboration and Effectiveness	Face-to-Face
7	Communication and Planning	Face-to-Face
8	Ethical and Legal Considerations	Online
9	Teaching with EPEC®-Pediatrics in the Face-to-Face Setting	Face-to-Face
10	Multimodal Analgesia	Online
11	Opioid Selection and Rotation	Online
12	Management of Neuropathic Pain and Adjuvant Analgesia	Online
13	Procedural Pain Management Strategies	Online
14	Chronic Complex Pain Management	Online
15	Management of Gastrointestinal Symptoms	Online
16	Management of Respiratory Symptoms	Online
17	Management of Emotional and Behavioral Symptoms	Online
18	Management of Neurologic Symptom	Online
19	Palliative Sedation	Online
20	Preparing for Imminent Death	Online
21	Integrative Medicine	Online
22	Introducing Quality Improvement to PPC	Online
23	Teaching Pain and Symptom Management	Face-to-Face
24	Methadone	Online

^a^Online for education of EPEC-Pediatric Trainers; all modules will be taught face-to-face to the End-User

While data on the effective dissemination of EPEC®-Pediatrics and EPEC™ is favorable [20], the impact on patient/family outcomes has not yet been measured. Recognition that education does not necessarily lead to significant improvements has led to a strong emphasis within the EPEC®-Pediatrics curriculum in each module to address “attitudes” (myths, misconceptions, obstacles) as well as providing a “skill” in addition to sharing “knowledge” in hopes of behavior changes among the Trainers and End-Users [23, 24]. To increase the chance of practice change toward better clinical pediatric care, the curriculum added the *Tailored Implementation of Practice Standards* (TIPS) Kit to the suite of resources available through EPEC™. Each TIPS Kit includes a protocol for an evidence-based clinical intervention (e.g. symptom management protocol), a guide for how to adapt the protocol to meet local needs, a template for evaluation measures, and detailed plans for quality improvement (QI) methods for implementation. TIPS Kits reduce the initial time investment needed to develop a QI project by providing a limited number of possible actions and measurement options to select from. The EPEC®-Pediatrics curriculum currently includes one TIPS Kit, which aims to standardize symptom assessment for children with serious illness using two pediatric versions of the Memorial Symptom Assessment Scale [25, 26].

In our study, the content of EPEC®-Pediatrics will not be changed; however, four key features will be added to the delivery process based on implementation science [27] to promote sustained improvement in the quality of palliative care for children with cancer and their families. 1) Rather than attending as individuals, Regional Teams of three to five health professionals representing oncology, palliative care, and the community (e.g., home care nurses, community pediatricians) will attend a Train-the-Trainer Conference together in 2015 and work as a team. 2) A second day will be added to the Conference to allow Regional Teams to review data collected in the pre-test period and use those data to develop regional dissemination strategies and plan their QI project. 3) The Research Team developed two additional TIPS Kits to provide a wider choice of QI projects. 4) Ongoing support will be provided by the Research Team for education and QI initiatives throughout the intervention period, 2015 - 2016. Teams will also communicate with each other via a listserv and webinars to share successes and challenges.

The effectiveness of our EPEC®-Pediatrics roll-out will be assessed according to four outcomes. The guiding research questions are: What is the impact of EPEC®-Pediatrics on: 1) the self-assessed knowledge of health professionals who take part in the curriculum; 2) knowledge transfer and dissemination outcomes; 3) practice change outcomes, and 4) the quality of palliative care provided to children with cancer and their families?

## Methods/design

### Design

In this study we will use a pre-post-test design and an integrated knowledge translation (KT) approach with involvement of knowledge users and key-stakeholders through the project [28]. The pre-test period will begin in January 2015 and the post-test period will begin in the fall of 2016. This timeline allows for the educational rollout of EPEC®-Pediatrics and QI to occur over approximately 15 months. Data collection and analysis will occur in three streams in order to answer the research questions: 1) knowledge dissemination, 2) quality improvement, and 3) care quality. The study has been approved by the Research Ethics Board (REB) at the Hospital for Sick Children (#1000047116) as the primary site as well as by the relevant REB for each participating site (See Additional file 1 for a list of sites with the corresponding REB).

### Stream 1 - Knowledge dissemination

Data collection and analysis in Stream 1 will address the impact of EPEC®-Pediatrics on the self-assessed knowledge of health professionals who take part in the curriculum and on knowledge transfer and dissemination outcomes.

#### Sample and procedure

The EPEC®-Pediatrics roll-out will include training of five Master Facilitators within Canada; Master Facilitators are individuals qualified to train future EPEC®-Pediatrics Trainers at the face-to-face conference. There are 3 steps to becoming a Master Facilitator: 1) become an EPEC®-Pediatrics Trainer by completing all 19 online modules and attending a face-to-face conference as a participant; 2) attend a Professional Development Workshop offered by EPEC for additional development of teaching skills, and finally 3) teach at an EPEC®-Pediatrics Train-the-Trainer conference where feedback is provided on teaching skills by existing Master Facilitators. At each of the 16 participating sites, 3 to 5 health professionals will be identified as Regional Team members. Each Regional Team member (*n* = 45-80) will become an EPEC®-Pediatrics Trainer through completion of 19 online-modules and 5 face-to-face modules. Two face-to-face sessions will be held over two full days with the content delivered by the new Canadian Master Facilitators in conjunction with the original developers of EPEC®-Pediatrics. Regional Teams will complete the online modules on their own, then attend one of the two-day sessions as a team. At the end of the face-to-face session the new Trainers will be asked to provide feedback on EPEC®-Pediatrics as a whole and assess their learning as part of the process. Feedback will be sought using a Knowledge Transfer and Exchange (KTE) Survey completed in paper based format.

Once Regional Team members have completed their training they will work to deliver aspects of the EPEC®-Pediatrics curriculum to End-Users at their local site. Trainers will be encouraged to think very broadly about who provides care to children with cancer within the institution where they are based, within the local community, and more broadly in the wider geographic area served by the hospital. Education sessions may be offered as part of existing structures (e.g., resident training session, education days for nurses, academic rounds, lunch and learns) or as separate sessions delivered specifically for the study. When End-Users attend an EPEC®-Pediatrics session, they will be provided with a consent form that gives details about our study. If they agree to take part, End-Users will be asked to complete the KTE Survey in hard copy to assess the impact of the session on knowledge transfer. Even if people in attendance do not want to take part in the research aspect of the session they are still welcome to attend. The Trainers who deliver the session will collect the surveys and submit them to the core study team via Research Electronic Data Capture (REDCap™) database, which is a secure, web-based application designed specifically for clinical research [29].

Regional Team members will be asked to complete an Education Roll-out Report on a quarterly basis to provide summary information about the education sessions they have delivered to local End-Users. The Report will be completed verbally with the Project Manager/Principal Investigators (PI) via telephone or Skype and data will be entered into REDCap™.

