#### Data collection tools

The KTE Survey was developed through the Canadian Partnership Against Cancer and is based on a tool developed by Skinner [30]. The survey includes items about the participants’ demographics (e.g., role, designation, organization type, province) and degree of agreement with statements that the information was relevant and useful, increased knowledge, and that stated learning objectives were met. There are also items asking whether the participant plans to discuss the information provided at the session with colleagues or use the information to make changes in practice.

The Education Roll-Out Report was developed by the study team to collect the number of times each EPEC®-Pediatrics module was offered along with the total number of attendees at the session and whether the session was held within the hospital or in the community. Regional Teams will be asked to comment on any successes and challenges in delivering the modules, indicate any ways that the study team could provide additional supports to assist in delivery of the modules and to describe plans for delivery of sessions in the coming quarter.

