#### Data analysis

Information obtained through the Education Roll-out Report and the KTE Surveys will be summarized descriptively. Our dissemination goal is to have a minimum of 5 Master Facilitators, 45 Trainers, and 600 End-Users from multiple professional groups across Canada (see Fig. 1) take part in at least one EPEC®-Pediatrics session. Our hypothesis is that the Trainers and End-Users will indicate that the sessions were useful, improved their knowledge related to the topic presented, and had some impact on their practice. We will compare the summarized responses to the Educational Report and KTE Surveys with these goals and hypotheses to determine if they have been achieved.

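### Trainers collect and submit the End-User surveys on their own sessions, which creates a risk of favourable bias in the End-User part of Stream 1

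*Protocol article*

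**What the plan says.** The route is set out in the protocol article under Stream 1, Sample and procedure. After consenting, "End-Users will be asked to complete the KTE Survey in hard copy to assess the impact of the session on knowledge transfer". Then "The Trainers who deliver the session will collect the surveys and submit them to the core study team", using the REDCap database.

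Under Data collection tools, the survey is said to record "degree of agreement with statements that the information was relevant and useful, increased knowledge, and that stated learning objectives were met", along with any plans to discuss the content with colleagues or to change practice. The demographic items given as examples are role, designation, type of organisation and province.

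The other Stream 1 tool, the Education Roll-out Report, is there to "collect the number of times each EPEC®-Pediatrics module was offered along with the total number of attendees at the session". It also records the setting and the Regional Team's comments.

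Under Data analysis, both tools are summarised descriptively and set against the goals and the hypothesis that "Trainers and End-Users will indicate that the sessions were useful, improved their knowledge related to the topic presented" and had some effect on practice. No numerical threshold for agreement is given.

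**The concern.** A Trainer has an interest in how a session is received, and here the Trainer is also the only described link between the respondent and the database. Two mechanisms follow.

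- **Courtesy.** A respondent who expects the teacher, often a local colleague, to see the form may answer more kindly.
- **Selective submission.** Forms can be lost, delayed or left out between the room and REDCap, and unfavourable forms may be lost more often.

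Both would move the result in the direction that the hypothesis predicts. More End-Users would not cure either of them. What is at stake is the answer, for End-Users, to the first research question (self-assessed knowledge), and the Discussion's statement that the design can measure this adequately.

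**Working it through.** The plan gives no figure to reproduce. Stream 1 has no sample size calculation, power or significance level; the sample size section belongs to Stream 3. The check is therefore a comparison of the relevant sections, followed by an illustration of scale.

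**1. Is the route stated, or only left open?** It is stated. The forms are on paper, REDCap is a web-based application, and the Trainers make the submission. Read plainly, the Trainer enters or uploads the forms and would ordinarily see them.

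**2. Is there another End-User measure?** None is described. The Education Roll-out Report holds counts, setting and team comments, with no End-User rating of knowledge or usefulness. The Regional Teams supply it themselves.

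**3. How far does the route reach?** It covers End-User sessions only. For the conference, the article says "At the end of the face-to-face session the new Trainers will be asked to provide feedback on EPEC®-Pediatrics as a whole", on paper, and does not give the Trainer collection route there. Stream 2 uses QI Progress Reports. Stream 3 uses parent and child surveys, health records and bereaved-parent surveys.

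**4. Do other surveys in the study use a different route?** Yes. In Stream 3, parents and children may answer through a REDCap link or with a Research Assistant. Bereaved parents may answer online, by mail, or by telephone with a Research Assistant at the central site.

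**5. Scale of selective submission (assumed inputs).** Let p be the true favourable share, and s the submission rate of unfavourable forms relative to favourable ones. The documents give neither value.

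Observed share = p / (p + (1 − p) × s)

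For p = 0.70 and s = 0.8: 0.70 / (0.70 + 0.30 × 0.8) = 0.70 / 0.94 = 0.745.

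| True share p | s = 1 | s = 0.9 | s = 0.8 | s = 0.5 |
|---|---|---|---|---|
| 50% | 50.0% | 52.6% | 55.6% | 66.7% |
| 70% | 70.0% | 72.2% | 74.5% | 82.4% |
| 90% | 90.0% | 90.9% | 91.8% | 94.7% |

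At s = 1 every form arrives and selection adds nothing; only a courtesy effect could remain. Over these values the inflation runs from 0 to 16.7 points (66.7 − 50.0). That range reflects the choice of s and is not an estimate for this study.

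**The case against.** The case for leaving the text alone has substance.

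- **The items rate the information more than the teacher.** They ask about relevance, usefulness, knowledge and learning objectives; no item on teaching skill is described. This weakens the courtesy pressure without removing it.
- **The forms may be anonymous.** No name is listed, and the form asks for the type of organisation, not which one. A condensed article may leave anonymity or folded forms to the full protocol, so silence on these is no fault. However, in a small local session, role and designation could still point to a person. Anonymity also would not prevent selective submission.
- **Paper collected in the room secures returns.** This is a fair reason for paper, and a link alone might trade one bias for another. It does not explain why the Trainer must be the one to submit the forms.
- **Attendance is already recorded.** A denominator therefore exists, but the article does not describe comparing it with the forms received.

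A reader might infer that the bias must exceed sampling error. With 600 respondents, 1.96 × √(p(1 − p)/600) is 3.7 points at p = 0.7 and 3.2 points at p = 0.8, so a shift of 5 to 10 points would be larger. The documents do not support this. The shift is a pure assumption. The 600 is a goal for people taking part in a session, and attendees may decline the survey. The formula also ignores grouping by session and site, and the plan claims no precision for this figure.

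**Conclusion.** The concern holds as a risk of favourable bias in the End-User part of Stream 1. It rests on a stated procedure, and on the KTE Survey being the only described End-User measure of knowledge and usefulness. The direction is the one the hypothesis favours. The size cannot be determined from the document; the tabulated values depend entirely on assumed p and s.

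A reader might go further and conclude that the whole Stream 1 hypothesis rests on compromised ratings, or that a study conclusion would change. Neither follows. The hypothesis also covers Trainers, whose conference surveys are not described as passing through this route. No agreement threshold is set, so no success criterion can be shown to flip. This is a minor, low-cost improvement.

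**What to change.** In Stream 1, Sample and procedure, replace the sentence on Trainer collection so that:

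1. End-Users complete the paper KTE Survey at the session and seal it in an envelope addressed to the core study team.
2. The core team enters the forms in REDCap.
3. Direct entry by the End-User through a REDCap link is offered as an option.

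In Stream 1, Data analysis, add that the number of forms received will be compared with the attendee counts in the Education Roll-out Report, and that the response rate will be reported per site. Because attendees may decline the survey, a shortfall will mix refusals with forms that never arrived, and the report should say so.

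The cost is envelopes, central data entry of the paper forms, and a possibly lower return rate where the link is used. Keeping sealed paper as the default preserves in-room completion.
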